
### Statistical analysis

Data will be expressed as mean and standard deviation for normally-distributed quantitative continuous variables or as median and interquartile range for non-normally-distributed quantitative variables and as frequencies and percentages for qualitative variables. Normality of distribution will be studied by applying the Shapiro-Wilk test and, accordingly, the change from baseline outcomes at 7 days will be compared between the control group and the intervention group by a Student’s t-test or the Wilcoxon T-test. Moreover, a multiple linear regression will be performed with the following dependent variables: sleep disruption, sleep efficiency, quality of life, caregiver overload, daytime sleepiness, physical activity, intensity and duration; and the following independent variables: the intervention, sex, age, educational level, marital status, time (hours a day) dedicated to care, if they receive care assistance, time they have been caring for, and relationship with the person they care for. The same procedure will be followed for the variables consumption of analgesics, anxiolytics and sleeping pills.

In the event that statistically significant results are obtained, in the cases of normally-distributed variables, 95% confidence intervals of the difference will be calculated to estimate between which values the difference is found. Statistical software SPSS 23.0 and Epidat 3.01 will be used. We will work with a confidence level of 95%, considering therefore, *p* values lower than 0.05 as statistically significant.

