## Abstract

**Background:**

Sleep disorders are commonly experienced by community caregivers for persons with cancer, with at least 72% reporting moderate to severe disorders. A consequence of this condition, which is associated with the presence of overload in the caregiver, is the increased risk of clinical depression. The aim of this study is to evaluate the effects of music on the sleep quality achieved by informal caregivers for cancer patients receiving home palliative care. In addition, we will assess the influence of specific variables that could modify these effects, analyse the correlates related to nocturnal wakefulness and consider the diurnal consequences according to the sleep characteristics identified.

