### Sample size

Based on the data published by Jespersen et al. 2015 [42] on sleep quality, it can be expected to find an effect equivalent to a standardized mean difference of 0.776; with an alpha error of 0.05 and a beta error of 0.10, the required sample size is two groups of 35 caregivers (Epidat 3.1), they will be increased to two groups of 40 in anticipation of possible losses.

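### The arms are compared on unadjusted change scores and the regressions leave out the outcome's baseline: a valid plan that gives up precision, and one that cannot show the effect modification named in the abstract

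*Protocol article*

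**What the plan says.** The Statistical analysis section states that "the change from baseline outcomes at 7 days will be compared between the control group and the intervention group", by Student's t-test or, for non-normal data, a Wilcoxon test. No adjustment is attached to this comparison.

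A multiple linear regression follows. Its independent variables are listed in full. They begin "the intervention, sex, age, educational level, marital status, time (hours a day) dedicated to care, if they receive care assistance" and end with time spent as a carer and relationship to the patient, so there are eight caregiver characteristics besides arm. Neither the outcome's baseline value nor any arm-by-variable term is on the list. The listed regression outcomes do not include PSQI sleep quality or total sleep time. The text does not say whether the regression outcome is the final value or the change.

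Baseline data exist. The section on outcome assessment describes a prior and a final assessment of all caregivers, PSQI at the start and end of the intervention, and accelerometry for 7 days before and 7 days during it.

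The Sample size section expects "an effect equivalent to a standardized mean difference of 0.776", "with an alpha error of 0.05 and a beta error of 0.10", giving 35 per group; "they will be increased to two groups of 40 in anticipation of possible losses".

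On modification, the Background part of the abstract says "we will assess the influence of specific variables that could modify these effects". The Aim section speaks only of evaluating the influence of specific variables.

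**The concern.** The pre-intervention value of an outcome is usually the strongest predictor of its later value. Subtracting it, as the change score does, uses it with a fixed coefficient of 1. ANCOVA estimates that coefficient and is at least as precise for any correlation below 1, apart from one degree of freedom. At the planned size of 35 to 40 per arm, the difference in precision could matter. For PSQI, on which the cited music review assessed sleep quality, the unadjusted change-score test is the only between-arm analysis specified, because PSQI is not among the regression outcomes.

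The second issue is separate. A regression without interaction terms estimates one common effect of music. Its coefficient for age or sex says whether that variable predicts the outcome, not whether it changes what music does. The abstract's promise therefore has no matching analysis.

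**Working it through.** **Inputs.** From the Sample size section: standardised difference 0.776, alpha 0.05, power 0.90, 35 per group raised to 40. Two-sided testing is assumed; it reproduces the stated size, whereas one-sided would give 29. The correlation rho is not in the protocol, so 0.3, 0.5 and 0.7 are assumed. Equal SDs at baseline and follow-up are also assumed.

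**1. The plan's own figure.** n per group = 2 × ((1.960 + 1.282)/0.776)² = 34.90, rounded up to 35. It reproduces. With the noncentral t, power at 35 per group is 89.3%, and at 40 per group 92.9%.

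**2. Variances**, in units of the raw-score SD:
- change score: SD = sqrt(2(1 − rho))
- ANCOVA: SD = sqrt(1 − rho²)
- variance ratio, ANCOVA to change score: (1 − rho²)/(2(1 − rho)) = (1 + rho)/2

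The change score therefore has 2/(1 + rho) times the ANCOVA variance: 54% more at rho 0.3, 33% more at 0.5 and 18% more at 0.7.

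**3. Power if 0.776 is in raw-score SD units** (noncentral t, two-sided 0.05). The effective difference is 0.776 divided by the SD from step 2.

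| rho | Effective difference, change / ANCOVA | 35 per arm, change vs ANCOVA | 40 per arm, change vs ANCOVA |
|---|---|---|---|
| 0.3 | 0.656 / 0.813 | 77.2% vs 91.8% | 82.6% vs 94.9% |
| 0.5 | 0.776 / 0.896 | 89.3% vs 95.9% | 92.9% vs 97.7% |
| 0.7 | 1.002 / 1.087 | 98.5% vs 99.4% | 99.3% vs 99.8% |

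**4. Power if 0.776 is in change-score SD units.** The change-score test then has 89.3% at 35 per arm whatever rho is. For ANCOVA the effective difference is 0.776/sqrt((1 + rho)/2):
- rho 0.3: 0.963, power 97.8%
- rho 0.5: 0.896, power 95.9%
- rho 0.7: 0.842, power 93.5%

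**5. What interactions could show.** For a modifier split 50/50, the standard error of the interaction is 4 × SD/sqrt(N), which is 0.478 SD at N = 70 and 0.447 SD at N = 80. By normal approximation:
- interaction as large as the main effect (0.776 SD): power 37% at N = 70, 41% at N = 80
- half that size (0.388 SD): 13% and 14%
- smallest interaction detectable with 80% power, (1.960 + 0.842) × SE: 1.34 SD and 1.25 SD

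**The case against.** The planned test is sound. Under randomisation, a comparison of change scores is unbiased, holds its error rate, and already uses the baseline by subtraction. ANCOVA improves efficiency but corrects no error. All of that stands, and it rules out several stronger readings.

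- A reader might infer that planned power holds only if rho is at least 0.5. That follows only if 0.776 is in raw-score SD units. The protocol says just that it is a standardised mean difference taken from a cited review. On the change-score reading, planned power holds at any rho.
- A reader might infer that the sample size is wrong. It reproduces on its own inputs.
- A reader might count regression to the mean from chance baseline imbalance as a further harm. Over randomisation, the imbalance averages to zero, and its effect is already in the change-score variance used above.
- The 77% figure combines the lowest rho shown, all planned losses and the less favourable reading of 0.776. With 40 per arm retained it is 83%.
- A reader might infer that a formal study objective has no analysis. Effect modification is named only in the abstract. The wording in the Aim section can be served by main effects, so the fault may be no more than a mismatch of wording.

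What survives is that the covariate list is spelled out and leaves baseline out, so this is not a detail left open for an analysis plan. Some precision is lost for any rho below 1.

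**Conclusion.** The point holds as a matter of efficiency, not validity. The loss at 35 per arm, on the raw-score reading, is about 15 percentage points of power at rho 0.3, 7 at 0.5 and 1 at 0.7. On the change-score reading no planned power is lost, but a gain of about 4 to 9 points is left unused. These sizes rest on an assumed rho and on equal SDs. The direction does not depend on the value of rho.

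The mismatch over effect modification does not depend on rho at all: the abstract says it will be assessed, and the stated regression cannot assess it. The trial is too small to do so with useful power. The change is worth making because it costs almost nothing, but the trial's main comparison is not unsound without it.

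**What to change.** 1. Make the main between-arm analysis an ANCOVA of the 7-day value on arm plus the baseline value of the same outcome. Apply it to the PSQI total score and to every other outcome measured at baseline.
2. Add the outcome's baseline value to each regression in the Statistical analysis section, and state whether the dependent variable is the final value or the change. With baseline in a linear model, the arm coefficient is the same either way. Step 2 alone would not reach PSQI or total sleep time, which are absent from the regression outcomes, so step 1 must name them or the list must be extended.
3. For effect modification, do one of two things. Either reword the abstract to match the Aim section, or add a few pre-named arm-by-variable interactions, reported with 95% confidence intervals, labelled exploratory and acknowledged as low-powered.

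The cost is a few sentences of analysis text, with no new data and no extra participants.

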### Study design

The study will consist in a single-blind, multicentre, randomised controlled trial. The study will be conducted at six Primary Care Clinical Management Units belonging to the Málaga-Guadalhorce Health District (Málaga, Spain), in informal caregivers of cancer patients receiving at-home palliative care. The caregivers, will be randomised into the experimental group (EG) or the control group (CG).

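### The non-normal fallback is named as the Wilcoxon T-test, a paired test, although it must compare two independent, unmatched arms

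*Protocol article*

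**What the plan says.** In the Statistical analysis section of the protocol article, the sentence that sets the rule states that "the change from baseline outcomes at 7 days will be compared between the control group and the intervention group". A Shapiro-Wilk check of normality decides which of two tests is used, and the article gives the pair as "t-test or the Wilcoxon T-test". The rank-sum or Mann-Whitney test is named nowhere in the article, and the version of Student's test is not given.

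The Study design and Randomisation sections allocate individual caregivers to a control or an intervention group, by cards in sealed envelopes. No matching or pairing is described. The Sample size section plans two groups for "an effect equivalent to a standardized mean difference of 0.776", at alpha 0.05 and 90% power. It arrives at 35 per group and raises this to 40 to allow for losses.

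The same Statistical analysis section adds a multiple linear regression with the intervention among the predictors. Its dependent variables are sleep disruption, sleep efficiency, quality of life, caregiver overload, daytime sleepiness and physical activity, and then medication use. Self-perceived sleep quality (the PSQI) and total sleep time are not listed. Confidence intervals are promised only for normally distributed variables with significant results.

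**The concern.** Wilcoxon's T is the statistic of the signed-rank test, which ranks differences within pairs. A between-arm comparison of change scores in unmatched caregivers has no pairs. The test that fits is the rank-sum (Mann-Whitney U) test.

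An analyst who follows the text in SPSS and picks the procedure of that name will land among the related-samples tests. The error therefore sits in the operative rule and is not just loose wording in the background. The PSQI is where it counts most. The effect size used for the sample size comes from a meta-analysis of sleep quality which, according to the Background section, was measured by the PSQI. If PSQI change fails the normality check, the misnamed test is the only between-arm analysis that the article states for it, and no confidence interval is planned beside it. The same is true of total sleep time.

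**Working it through.** **1. Is the design an independent two-group comparison?** Inputs from the Sample size section: standardised difference d = 0.776, alpha 0.05 (taken as two-sided, since sidedness is not stated), power 0.90.

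n per arm = 2 × (z₀.₉₇₅ + z₀.₉₀)² / d² = 2 × (1.960 + 1.282)² / 0.776² = 21.01 / 0.602 = 34.9, so 35.

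This reproduces the plan's 35. A one-sided alpha gives 29, which does not match. The figure is thus an independent-groups calculation, in line with the Study design section. The rise to 40 allows for 5/40 = 12.5% losses.

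**2. Can the named test be run between the arms?**
- *Unequal arms.* With 33 against 35 values the signed-rank test cannot be computed, because two values have no partner. The plan expects losses, so unequal arms are likely.
- *Equal arms.* Pairs must be invented. In one simulated data set (35 per arm, lognormal changes, shift 0.5 SD), 2,000 random pairings gave p from 0.000004 to 0.005, where Mann-Whitney gives the single value 0.00001. In a second simulated set with Mann-Whitney p = 0.24, the central 95% of signed-rank p values ran from 0.09 to 0.40. Neither range crosses 0.05. They show that the result depends on row order, not how often a conclusion would flip.

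**3. Long-run behaviour.** 4,000 runs per setting, 35 per arm. The distributions of change are assumptions, as the article gives none.

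| Change distribution | Type I error, rank-sum | Type I error, arbitrary pairs | Power at 0.776, rank-sum | Power at 0.776, arbitrary pairs |
|---|---|---|---|---|
| Normal | 4.8% | 4.8% | 87.8% | 87.6% |
| Lognormal | 4.5% | 4.3% | about 100% | 99.4% |
| t, 3 df | 5.2% | 5.2% | 98.6% | 96.6% |

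Arbitrary pairing made blind to outcome keeps the error rate and costs little power. The defect is that the result is not reproducible and cannot be computed with unequal arms. It is not an inflated false-positive rate.

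**4. Does the Shapiro-Wilk step do harm?** With the rank-sum test as fallback, and the check applied to each arm, the two-stage rule had type I error of 4.9% (normal), 4.5% (lognormal) and 5.4% (t, 3 df). It flagged at least one arm in 11% of runs with truly normal data and no difference, so the fallback can be reached even without real non-normality.

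**5. Does the correction change the sample size?** With the rank-sum test's efficiency of 0.955 relative to the t-test under normality, 35 / 0.955 = 36.6, so 37 per arm. At its worst-case efficiency of 0.864, 35 / 0.864 = 40.5, so 41. The planned 40 covers the first before losses and falls one short of the second. Under the non-normal shapes tried above, power with only 35 per arm was 98.6% or more.

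**The case against.** The strongest reply is that this is a misnomer. The sentence says the change is compared between the groups and sets the test beside Student's t-test, which points to the Wilcoxon rank-sum test. That is plausible, and if so only the name is wrong. It does not remove the point, because the letter T belongs to the paired statistic and no other sentence in the article corrects it.

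Three stronger readings are tempting, and the documents do not support them.

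- *A reader might infer that the plan will run before-after tests within each arm and compare their significance.* That would be a serious fault, but the sentence specifies a comparison between the groups. Error rates worked out for the within-arm procedure describe something that the article does not propose.
- *A reader might infer that the Shapiro-Wilk pre-test itself invalidates the comparison.* Step 4 shows no material inflation. What remains is that the test and the summary measure are chosen from the data, which is a matter of preference.
- *A reader might infer that no non-normal outcome gets a valid between-arm analysis.* The regression includes the intervention as a predictor and gives a between-arm estimate for most outcomes whichever branch is taken. Only outcomes that it omits, notably the PSQI and total sleep time, depend on the fallback alone.

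It is also fair to say that the likelihood of reaching the fallback for the PSQI is unknown. The check concerns the change score, for which the article gives no distribution.

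**Conclusion.** The point holds in a limited form. The named fallback is a paired test and the comparison is between independent, unmatched arms. As written, it cannot be computed with unequal arms and has no unique p value with equal ones. The consequence is greatest for the PSQI and total sleep time, which have no other stated between-arm analysis in the non-normal branch. It is more than clerical because it sits in the rule that an analyst would follow. It does not undermine the design, the sample size or the other outcomes' regression. The conclusion rests on the ordinary meaning of Wilcoxon T and on the absence of any described matching. The simulated figures are illustrative, and the conclusion does not depend on them.

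**What to change.** In the Statistical analysis section, replace Wilcoxon T-test with Mann-Whitney U (Wilcoxon rank-sum) test, and state that Student's t-test is the independent-samples version. This is one sentence; SPSS runs both tests and the planned 40 per arm can stay. It should be settled before the data are analysed.

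Replacing the Shapiro-Wilk rule with a single pre-specified analysis, such as a baseline-adjusted model that also covers the PSQI and total sleep time, would give an effect estimate whatever the distribution. That is optional and goes further than this defect requires.

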## Methods / design

### Aim

The aim of the study is to assess the effects of music on sleep quality in informal caregivers of cancer patients receiving home palliative care, and to evaluate the influence of specific variables. Specific aims are the following:
To assess the following sleep quality parameters in caregivers:
Sleep quality.Total sleep time and rest time.Sleep disruption.Sleep efficiency.To assess the following parameters related to wakefulness and daytime consequences, according to the sleep characteristics considered:
Psychological results: i) Quality of life; ii) Caregiver overload.Physical results: i) Daytime sleepiness; ii) Physical activity (intensity and duration).To assess the caregivers’ satisfaction with the intervention.

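### Eight caregiver characteristics in about seven regressions under one p<0.05 rule: about three chance findings are expected if none matters, so these coefficients should be labelled exploratory

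*Protocol article*

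**What the plan says.** The Aim section sets out to study the effect of music on sleep quality "and to evaluate the influence of specific variables". The Abstract words the same aim as variables able to alter the effect of music, and adds an analysis of factors associated with being awake at night.

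The Statistical analysis section first compares change between the arms with a t-test or a Wilcoxon test. It then adds a multiple linear regression per outcome. The outcomes are disrupted sleep, sleep efficiency, quality of life, overload, sleepiness by day, and physical activity with its intensity and duration. The predictors open with "and the following independent variables: the intervention, sex, age, educational level, marital status, time (hours a day) dedicated to care" and end with "if they receive care assistance, time they have been caring for, and relationship with the person they care for". That makes eight caregiver characteristics besides the intervention. Use of analgesics, anxiolytics and sleeping pills is to be handled in the same way.

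One rule closes the section: p "values lower than 0.05 as statistically significant". No regression is named as primary and no coefficient is called exploratory. Confidence intervals are promised only for differences, and only after a significant result.

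**The concern.** The regressions are the only analysis in that section in which the caregiver characteristics appear, so only their coefficients can serve the aim on influencing variables. Read together, the aim and the blanket threshold invite the authors to report every characteristic with p below 0.05 as an influence on sleep, overload or activity.

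With many such tests on one small sample, some will cross the threshold by chance. The plan gives no way to tell those from real associations, and promises no interval for a characteristic that would show how imprecise its estimate is. At stake is the credibility of the secondary findings on who sleeps badly or is overburdened, not the comparison of music with control.

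**Working it through.** **The plan's own figure.** The Sample size section assumes "an effect equivalent to a standardized mean difference of 0.776", "with an alpha error of 0.05 and a beta error of 0.10". With the two-sided normal formula, n per group = 2 × ((1.960 + 1.282) / 0.776)² = 34.9, so 35. The stated 35 per group is reproduced. It is sized for a two-group difference, not for the regression coefficients. The recruited number follows from "they will be increased to two groups of 40 in anticipation of possible losses", so 70 to 80 caregivers will be analysed.

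**Inputs for the check.**
- Characteristics per model: 8 (counted from the list in Statistical analysis).
- Outcomes: 7 on the middle reading. The range is 6 to 8, depending on whether physical activity, intensity and duration count as one, two or three outcomes. If the three drug variables are further outcomes, it is 10 (range 9 to 11).
- Threshold: 0.05 for each test.
- Correlation between outcomes: not given in the article, so assumed at 0 to 0.7.

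**Expected number of chance findings** = 8 × outcomes × 0.05, if no characteristic matters and each test holds its 5% level. This does not depend on the correlation between outcomes.

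| Outcomes | Tests | Expected by chance |
|---|---|---|
| 6 | 48 | 2.4 |
| 7 | 56 | 2.8 |
| 8 | 64 | 3.2 |
| 10 | 80 | 4.0 |
| 11 | 88 | 4.4 |

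**Chance of at least one.** If the tests were independent, it is 1 − 0.95^56 = 0.943 for 56 tests and 1 − 0.95^80 = 0.983 for 80. The outcomes come from the same caregivers, so the value was also simulated: least squares with intercept, arm and eight characteristics, 70 caregivers, characteristics mutually correlated at 0.2, no true effects, 3,000 runs per setting.

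| Outcome correlation | 7 outcomes | 10 outcomes |
|---|---|---|
| 0 | 93.0% | 97.6% |
| 0.3 | 91.1% | 95.7% |
| 0.5 | 87.1% | 91.7% |
| 0.7 | 75.4% | 81.2% |

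Simulation error is below one percentage point; at 75.4% the standard error is √(0.754 × 0.246 / 3,000) = 0.8 points.

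**Sensitivity to coding.** The table counts one test per characteristic. If education, marital status and relationship each had three levels and every printed coefficient were tested, there would be 11 per model: 77 for seven outcomes and 110 for ten. The expected counts are then 77 × 0.05 = 3.85 and 110 × 0.05 = 5.5. The simulated chance of at least one runs from 96% (correlation 0) to 82% (0.7) with seven outcomes, and from nearly 100% to 88% with ten.

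**Can these models answer the Abstract's question?** A variable modifies the effect if the effect of music differs across its levels. That needs an intervention-by-variable term. The predictor list contains main effects only, so a significant characteristic says nothing about effect modification, whatever error control is used.

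**The case against.** The strongest objection is that the text never says each characteristic will be tested or reported as a finding. The intervention heads the predictor list, which fits ordinary covariate adjustment, and the only reporting instruction concerns intervals for a difference. This stands to the extent that testing is inferred. The inference is still well supported: the Aim names these variables, the arms are already compared outside the regressions, and no other analysis uses the characteristics. If only adjustment was meant, one sentence settles it.

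A second objection is that multiplicity rules for secondary models commonly sit in an analysis plan, which is not shown here. That is fair: the lack of such a rule would be no finding by itself. The point is the rule that is stated, which calls every p below 0.05 significant without restriction, beside an aim that makes the characteristics of interest.

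Third, the drug-use sentence is ambiguous. The section on outcome assessment lists drug consumption among the independent variables, so three further outcomes are not certain. This stands; 56 tests is therefore the main figure and 80 the upper reading.

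A reader might infer more than the documents support:
- *That chance findings are all but certain.* This would need nearly independent tests and no true influence of any characteristic. The first is unlikely for related outcomes such as sleep disruption and efficiency. The second is a benchmark, doubtful for example for daily care hours and overload.
- *That eight covariates weaken the estimate of the music effect, so the list should be cut.* Any loss depends on how the characteristics are coded and how much of the outcome they explain, and the article gives neither. The planned t-test or Wilcoxon comparison does not use the model, and the PSQI is not among its listed outcomes. The covariates are already named in advance, so a shorter list is a preference.

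**Conclusion.** The concern holds in a limited form. Under the stated rule, about 2.8 of 56 covariate tests (4.0 of 80 on the wider reading) will be significant by chance if no characteristic matters. At least one will be so with a probability of roughly 75% to 98%.

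The expected count rests on the no-influence benchmark and on tests that hold their level. The probability also rests on assumed outcome correlations of 0.7 to 0. If some characteristics do matter, the expected number of false findings shrinks in proportion to the tests that remain null. With half of the 56 null, for example, it is 28 × 0.05 = 1.4, still mixed in with the real ones.

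The comparison of change between arms, including the PSQI, is not affected. The point deserves a change of wording before analysis, because a restriction added after the results are seen would look driven by them.

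**What to change.** Add two statements to Statistical analysis. First, in the multiple regressions the 0.05 rule applies to the intervention coefficient only. Second, the coefficients of the caregiver characteristics are exploratory and will be reported as estimates with 95% confidence intervals, whether or not they are significant, and without a significance claim.

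If claims about characteristics are wanted, apply Benjamini-Hochberg control of the false discovery rate over all characteristic-by-outcome tests. That requires the family to be fixed first: say how many activity outcomes there are, and whether the three drug variables are outcomes.

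State also that main-effect coefficients will not be presented as evidence on which variables modify the effect of music, since no interaction term is listed.

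The cost is wording only; recruitment, visits and data collection are unchanged. The downside is that the report can no longer list significant predictors from these models without error control.

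### The 95% confidence interval of the group difference is planned only for significant, normally distributed outcomes, so a null or non-normal result has no planned interval

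*Protocol article*

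**What the plan says.** All of the relevant text on analysis is in the Statistical analysis section of the protocol article.

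- Choice of test: "Normality of distribution will be studied by applying the Shapiro-Wilk test", and depending on the result "the change from baseline outcomes at 7 days will be compared between the control group and the intervention group" with a Student's t-test or a Wilcoxon test.
- Interval: "In the event that statistically significant results are obtained, in the cases of normally-distributed variables, 95% confidence intervals of the difference will be calculated". The stated purpose is "to estimate between which values the difference is found".
- Non-normal variables: the only summary promised is the "median and interquartile range for non-normally-distributed quantitative variables".
- Regression: "a multiple linear regression will be performed with the following dependent variables: sleep disruption, sleep efficiency, quality of life, caregiver overload, daytime sleepiness", followed by physical activity. The intervention is one of the predictors. No interval is stated for the coefficients, and neither PSQI sleep quality nor total sleep time is in the list.

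The Sample size section bases the trial on sleep quality and expects "an effect equivalent to a standardized mean difference of 0.776", with alpha 0.05 and beta 0.10. That gives 35 caregivers per group, raised to 40 for losses.

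**The concern.** The protocol treats the interval as a follow-up to a significant test. Its more important use is the opposite case. When a difference is not significant, the interval shows whether a worthwhile benefit has been ruled out or whether the data are compatible with both no effect and the planned effect. Under the stated rule these two situations would be reported alike.

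The second condition is a separate gap. If Shapiro-Wilk sends an outcome to the Wilcoxon test, no interval is planned even when the result is significant. Median and interquartile range describe each arm; they are not an interval for the treatment difference.

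This is a stated rule, not a detail that an article would leave to a fuller document. An analysis plan that followed it would carry it forward. PSQI sleep quality is most exposed, because the two-group comparison is the only analysis described for it that could yield an effect estimate.

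**Working it through.** **Inputs.** From the Sample size section: standardised difference 0.776, alpha 0.05, beta 0.10, 35 per group needed, 40 per group recruited. From the Statistical analysis section: significance at p below 0.05 and 95% confidence. Sidedness is not stated; two-sided is assumed, and step 1 supports this. True effects other than 0.776 are assumptions chosen to show a range.

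**1. The protocol's own figure.** n per group = 2 × (1.960 + 1.282)² / 0.776² = 2 × 10.507 / 0.6022 = 34.9, so 35. This matches. A one-sided calculation gives 29, so the stated figure is two-sided.

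**2. Width of the interval.** In SD units the half-width is t(0.975, 2n − 2) × √(2/n).

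- n = 35: 1.9955 × 0.2390 = 0.477
- n = 40: 1.9908 × 0.2236 = 0.445

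**3. What the interval would settle in a null trial.** A result is non-significant when the estimate lies within one half-width of zero. It also excludes the planned effect when the estimate plus the half-width is below 0.776.

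- n = 35: 0.776 − 0.477 = 0.299. A null estimate below about 0.30 SD excludes the planned effect; one between 0.30 and 0.477 SD does not.
- n = 40: 0.776 − 0.445 = 0.331. The division falls at about 0.33 SD.

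Both kinds of null result can occur, and the rule withholds the figure that separates them.

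**4. How often no interval is planned.** For a normal outcome this is the probability of a non-significant two-sample t-test, 1 − power. Power comes from the noncentral t distribution with 2n − 2 degrees of freedom and noncentrality d√(n/2). A simulation of 200,000 trials per scenario gives the same values.

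| True effect (SD) | No interval, n = 35 | No interval, n = 40 |
|---|---|---|
| 0.776 (planned) | 11% | 7% |
| 0.5 (assumed) | 46% | 40% |
| 0.3 (assumed) | 76% | 74% |
| 0.2 (assumed) | 87% | 86% |
| 0 (assumed) | 95% | 95% |

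For an outcome judged non-normal the figure is 100% at every true effect.

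**5. The intervals that are shown.** The same simulation, restricted to significant trials at n = 35:

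| True effect (SD) | Mean estimate | Coverage of the displayed interval |
|---|---|---|
| 0.776 | 0.825 | 97% |
| 0.5 | 0.67 | 95% |
| 0.3 | 0.605 | 89% |
| 0.2 | 0.56 | 79% |

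At a true effect of zero the coverage is 0%, because an interval shown only after p < 0.05 always excludes zero. Across all trials, significant or not, coverage is 95% at every true effect.

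**The case against.** **Exaggerated estimates.** A reader might infer from step 5 that the rule makes estimates too large and intervals unreliable. The documents do not support that. For a significant, normally distributed outcome the present rule and the fix give the same estimate and the same interval. The inflation comes from looking only at significant results, and it would remain in those trials after the fix. At the protocol's own 0.776 SD it is small: 0.825 / 0.776 = 1.06, about 6%, with coverage of 97%. Coverage falls clearly below 95% only at smaller true effects, which the document does not assume. What stands is narrower: across the many outcomes listed, a table with intervals for the significant ones alone is a selected set.

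**An uninterpretable null.** A reader might also infer that a null report could not distinguish no effect from too small a trial. That goes too far. Means and standard deviations are promised for normal variables without a significance condition. If they are given by arm for the change scores, a reader can rebuild the interval. The section does not say that the summaries are of change, however, and medians with interquartile ranges do not allow the same rebuild.

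**Other routes to an interval.** The restriction most naturally applies to the two-group comparison and need not bar intervals for regression coefficients, and software may print intervals by default. Neither is promised, and the regression list does not include PSQI sleep quality.

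**Seriousness.** Randomisation, data collection, sample size and the tests are untouched, and the intervals can be computed later from the same data. This stands, and it limits the grade of the point.

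**Conclusion.** The point holds as one of estimation and reporting, to be graded as should-fix. As written, the protocol plans a 95% interval for the group difference only when the test is significant and the variable is normal. A null or non-normal result, including one on PSQI sleep quality, has none. At 35 per arm, a normal outcome is left without an interval in about one trial in nine if the planned effect is true, and in about three in four if the true effect is 0.3 SD. These shares assume a two-sided t-test at 0.05 with equal variances, and effects other than 0.776 are illustrative.

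The rule does not change the type I error of any test, and it does not alter the interval of any individual significant normal outcome. It also does not make a null result impossible to interpret; it leaves out the figure that would make interpretation direct.

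**What to change.** Replace the conditional sentence in the Statistical analysis section with wording such as:

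> The between-group difference with its 95% confidence interval will be reported for every outcome, regardless of p value or distribution: the mean difference for normally distributed variables, a Hodges-Lehmann or bootstrap interval otherwise, and regression coefficients with their 95% confidence intervals.

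This should be settled before the data are analysed, so that which intervals appear does not depend on the results. It needs no further participants, visits or data, and no test changes. The cost is one sentence and a few more table columns.
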